### 3 Study Design

#### 3.1 General Design

The trial is an open label unmasked non-randomized single-armed trial where all enrolled dogs will receive treatment. The trial will evaluate whether preconditioning lymphodepletion with doxorubicin will improve response rates to inhaled IL-15 in dogs with lung metastases.

The trial will consist of the following phases:

Screening, enrollment, lymphodepletion (doxorubicin administration), treatment with investigational agent (IL-15), assessment for response, long-term follow-up/monitoring for disease progression.

The expected duration of subject participation is 98 days, but may be longer if decided by the PI and pet owner.

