### ***1.1 Background***

Previous trials have found that inhaled IL-15 is well tolerated and resulted in durable responses in dogs with metastatic melanoma or osteosarcoma. Analyses of correlative data found that dogs with low lymphocyte counts were more likely to achieve clinical benefit from this therapy. The goal for this study is to determine whether lymphodepletion with doxorubicin prior to initiating inhaled IL-15 might improve response rates in canine patients with metastatic tumors to the lung. The primary endpoints of this study are to determine the safety and preliminary evidence of efficacy for this combination treatment. Toxicity, response, and progression will be evaluated based on modified versions of the VCOG consensus documents for adverse events and RECIST criteria for solid tumors.

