#### 3.2 Primary Study Endpoints

Objective response rates based on radiographic response

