## **5 Subject Selection and Withdrawal**

### **5.1 Inclusion Criteria**

#### Canine:

In order to be eligible for trial participation, the subject must:

1. Present with one or more pulmonary nodules measuring at least 1cm on radiographs consistent with metastatic disease from cytologically or histologically confirmed osteosarcoma or melanoma
2. Adequate local control of primary tumor (i.e. surgery or radiation)
3. Radiographs performed within 7 days of enrollment (Day 0)
4. Dogs > 1 year
5. Body Weight > 15 kg
6. VCOG-CTCAE v2 constitutional clinical signs < grade 2
7. Overseeing clinician deems dog able to undergo sedation for radiographs
8. CBC and Chemistry performed within 7 days of enrollment (Day 0) showing adequate organ function:
  - a. HCT > 25%, Neutrophil Count > 2,000/ul, Platelet Count > 75,000/ul,
  - b. Creatinine < ULN; bilirubin < ULN; ALT < ULN; AST < ULN
9. Urinalysis performed within 7 days of enrollment (Day 0)
10. Owner consent for dog's inclusion into the trial

CONFIDENTIAL

This material is the property of the University of California Do not disclose or use except as authorized in writing by the study sponsor

Caretaker:

In order to be eligible for participation, the pet's caregiver must be:

1.  $\geq 18$  years of age on the day of signing the informed consent
2. Able to understand the requirements of the study as determined by the investigators or research assistants
3. Able to give informed consent for on behalf of the dog for inclusion in the study
4. Able to read, understand and fill out the questionnaires
5. Able to administer trial treatment to their dog as demonstrated at the first visit

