### 6.3 Assigning Subjects to Treatment Groups

N/A, single-arm study, no masking or randomization

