## 8 Statistical Plan

### 8.1 *Sample Size Determination*

Hypothesizing an improvement in ORR from 11% to 50% using conditioning chemotherapy, a sample size of 10 provides 80% power to detect this difference between our historical ORR (the null hypothesis) and the higher ORR of interest at the 0.05 level (1-sided). Therefore, using this study design, it is unlikely that treatments producing modest improvements in ORR will be selected for follow up testing

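### The radiographic primary endpoint has no masked reading, and with ten dogs one upgraded dog can decide the test against the historical 11%

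*Protocol*

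**What the plan says.** Section 3.1 describes the design: "The trial is an open label unmasked non-randomized single-armed trial where all enrolled dogs will receive treatment". Section 6.3 (treatment assignment) reads "N/A, single-arm study, no masking or randomization", and section 6.6 marks blinding of the product as not applicable.

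The only primary endpoint, in section 3.2, is "Objective response rates based on radiographic response". Section 1.1 says that toxicity, response and progression are "evaluated based on modified versions of the VCOG consensus documents for adverse events and RECIST criteria for solid tumors", but gives neither the modification nor any percentage cut-off. Under section 5.1, item 1, a dog qualifies with "one or more pulmonary nodules measuring at least 1cm on radiographs".

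Thoracic radiographs are scheduled at Day 0, Day 35, Day 49 and follow-up (section 7.1). Sections 7.2.6 and 7.2.7 label the Day 35 and Day 49 visits as response evaluation. No section names the reader, the reading order, or a masked or independent read.

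Section 8.1 sets the test: "Hypothesizing an improvement in ORR from 11% to 50% using conditioning chemotherapy", where "a sample size of 10 provides 80% power to detect this difference" at a one-sided 0.05 level.

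**The concern.** With one arm there is no allocation to conceal. What can still be concealed is the time point of each film, and that matters here because the endpoint is a measured change from baseline. A reader who knows which film follows treatment may, without intending to, measure its nodules as smaller. The result is compared with a fixed historical rate, so there is no concurrent group read by the same person in which the tendency would show or cancel.

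The plan as written leads naturally to response being judged in real time at the visits, by someone who knows the visit. With ten dogs the count that separates success from failure is small, so a few borderline readings carry the conclusion. At stake is a false signal for the combination, or a true one that cannot be defended against this criticism.

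**Working it through.** **Inputs.** N = 10, null rate 0.11, alternative 0.50, one-sided level 0.05 (section 8.1). All ten dogs are taken as evaluable; section 8.3 restricts the analysis to dogs that start inhaled IL-15.

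**Step 1: reproduce the plan's figure.** Exact binomial, P(X ≥ r | 10, p) = Σ from x = r to 10 of C(10, x) p^x (1 − p)^(10 − x).

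| Responders required | P under 11% | P under 50% |
|---|---|---|
| 3 | 0.0884 | 0.945 |
| 4 | 0.0178 | 0.828 |
| 5 | 0.0025 | 0.623 |

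The smallest count with a one-sided level of at most 0.05 is 4, with power 0.828. That agrees with the stated 80%. The protocol gives no pass mark, so 4 is derived here.

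**Step 2: effect of one dog.** Three responders give p = 0.0884 and fail; four give p = 0.0178 and pass. If one non-responder were always upgraded, three true responders would suffice and type I error would be 0.0884.

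**Step 3: how often the trial sits on that edge.** P(X = 3) = C(10, 3) p³ (1 − p)⁷.

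- p = 0.11: 0.071
- p = 0.20: 120 × 0.008 × 0.2097 = 0.201
- p = 0.30: 120 × 0.027 × 0.0824 = 0.267
- p = 0.35: 120 × 0.0429 × 0.0490 = 0.252
- p = 0.50: 0.117

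The edge is most likely at moderate true rates, and section 8.1 says that modest improvements are unlikely to be taken forward.

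**Step 4: systematic misreading.** Assume each non-responder independently has probability m of being scored as a response, and true responders are always scored correctly. Under the null, the observed rate is q = 0.11 + 0.89 m. The documents give no value for m, so a range is shown.

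| m | q | P(X ≥ 4 given q) |
|---|---|---|
| 0 | 0.110 | 0.018 |
| 2% | 0.1278 | 0.030 |
| 5% | 0.1545 | 0.055 |
| 10% | 0.199 | 0.119 |

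The nominal 0.05 is crossed somewhere between 2% and 5%.

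**Step 5: what a misreading means in millimetres.** No shrinkage cut-off is stated. For assumed cut-offs of 20% to 50%, a single 10 mm nodule needs a change of 2 to 5 mm, and a 30 mm nodule 6 to 15 mm.

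**The case against.** The masking statements can be read as being about treatment only. Section 3.1 describes allocation, section 6.3 concerns assignment to groups, and not applicable is the correct entry in section 6.6 for one open arm. On that reading the protocol is silent on film reading, which an imaging manual or analysis plan might cover. This stands in part. A reader might infer that films are to be measured in sequence by someone who knows which is pre-treatment, but the protocol does not say so. It does call the trial unmasked and place response evaluation at the visits, with nothing pointing the other way.

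A reader might also infer that the trial rests on 1 cm lesions, so that a millimetre of bias decides it. The documents do not support that. One centimetre is the entry minimum, lesions may be larger or multiple, and neither the cut-off nor the reading error is given.

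Sensitivity to one dog is a property of any ten-subject test, and discreteness leaves slack: the actual level is 0.018, and 2% misreading keeps it at 0.030. Both points are correct. They limit the size of the problem but do not remove it.

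Finally, the films behind the historical 11% may themselves have been read unmasked, in which case similar bias could already sit in the null rate. Section 8.1 does not say. So it cannot be claimed that all reading bias passes undiluted into the comparison, and the historical method needs to be stated.

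**Conclusion.** The point holds in limited form. The protocol provides no masked reading of its only primary endpoint, and at N = 10 the derived boundary between 3 and 4 responders (p = 0.088 against 0.018) means one upgraded dog can decide the test. For that to happen, exactly three dogs must truly respond and a further dog must be misread. The first condition alone has probability 0.071 at a true rate of 11%, and 0.20 to 0.27 at the true rates of 20%, 30% and 35% examined.

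Under the assumed misreading range of 2% to 10% per non-responder, type I error is 0.030 to 0.119 rather than 0.018. These figures rest on ten evaluable dogs, the derived pass mark, independent misreadings, and a historical rate free of the same bias.

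This is an inexpensive improvement in how the endpoint is measured. It is not an error in the sample size, which reproduces, and it is not evidence that biased reading is planned.

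**What to change.** In sections 3.2 and 7.2, state the following for the response rate:

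1. Whoever already measures the films does so once per dog, after the Day 98 follow-up film or the last film if that is earlier. A fixed end is needed because follow-up may continue beyond Day 98.
2. The coordinator removes dates and visit labels and presents the films in random order. All measurable nodules are recorded on each film.
3. These measurements are locked. Only then is film order restored, target lesions taken from the Day 0 film, new lesions identified, and response and response duration derived by the protocol's modified RECIST.
4. The real-time read serves clinical care only and does not feed the response rate.
5. Section 8.1 states how the films behind the historical 11% were read, so that any difference in method is disclosed.

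**Cost.** About 30 to 40 film sets (10 dogs × 3 to 4 films), a few hours of re-reading, and a later final response rate. No extra reader, visit, film or dog is needed. Masking will be imperfect if the reader recalls a dog or if the shrinkage is large enough to reveal the order. If the historical films were read unmasked, the two rates will differ in method, which is why item 5 is needed.

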#### 3.2 Primary Study Endpoints

Objective response rates based on radiographic response

#### 3.3 Secondary Study Endpoints

Response duration, toxicity

#### 3.4 Primary Safety Endpoints

Based on VCOG and known toxicity of doxorubicin. Toxicity will be assessed using client completed forms along with physical exam, temperature, CBC, Chemistry panel, urinalyses.

### 4 Study Site(s), Staff, and Facilities

#### 4.1 Study Site(s)

Single site; Veterinary Medical Teaching Hospital, School of Veterinary Medicine, University of California-Davis

### **4.3 Study Facilities**

#### **4.3.1 Clinical Research Area**

Veterinary Medical Teaching Hospital, School of Veterinary Medicine, University of California-Davis; CCAH

#### **4.3.2 Document Storage**

Paper CRF records in a study binder will be kept in Oncology. Following patient completion, the paper source records will be scanned and saved in a shared Box folder. Patient and client identifying information will be redacted. Additionally, UC Davis will maintain its own abbreviated REDCap database. The UCD REDCap will be used to electronically collect QOL surveys from pet owners. Adverse Events will also be entered into this database for ease of analysis. Basic patient and owner information (ID numbers, e-mails, etc.) will be included to facilitate submission of survey.

#### **4.3.3 Laboratory Services**

Routine laboratory tests will be submitted through the VMTH with study number for billing purposes.

#### **4.3.4 Research Sample Storage**

[N/A.]

## **5 Subject Selection and Withdrawal**

### **5.1 Inclusion Criteria**

#### Canine:

In order to be eligible for trial participation, the subject must:

1. Present with one or more pulmonary nodules measuring at least 1cm on radiographs consistent with metastatic disease from cytologically or histologically confirmed osteosarcoma or melanoma
2. Adequate local control of primary tumor (i.e. surgery or radiation)
3. Radiographs performed within 7 days of enrollment (Day 0)
4. Dogs > 1 year
5. Body Weight > 15 kg
6. VCOG-CTCAE v2 constitutional clinical signs < grade 2
7. Overseeing clinician deems dog able to undergo sedation for radiographs
8. CBC and Chemistry performed within 7 days of enrollment (Day 0) showing adequate organ function:
  - a. HCT > 25%, Neutrophil Count > 2,000/ul, Platelet Count > 75,000/ul,
  - b. Creatinine < ULN; bilirubin < ULN; ALT < ULN; AST < ULN
9. Urinalysis performed within 7 days of enrollment (Day 0)
10. Owner consent for dog's inclusion into the trial

CONFIDENTIAL

This material is the property of the University of California Do not disclose or use except as authorized in writing by the study sponsor

Caretaker:

In order to be eligible for participation, the pet's caregiver must be:

1.  $\geq 18$  years of age on the day of signing the informed consent
2. Able to understand the requirements of the study as determined by the investigators or research assistants
3. Able to give informed consent for on behalf of the dog for inclusion in the study
4. Able to read, understand and fill out the questionnaires
5. Able to administer trial treatment to their dog as demonstrated at the first visit

## **5.2 Exclusion Criteria**

1. Owner unable or unwilling to administer inhaled IL-15 twice daily and/or dog unable to tolerate twice daily nebulization
2. Prior IL-15 therapy
3. Chemotherapy within 2 weeks of Day 0 (prior doxorubicin is acceptable)
4. Immunotherapy or radiation therapy within 2 weeks of Day 0
5. Surgery within 2 weeks of Day 0
6. Known or suspected MDR mutation
7. Cardiac disease precluding doxorubicin as determined by the clinician
8. Concurrent therapy\*\*
  - 8.1.\*\*Exceptions: NSAIDS for pain control acceptable if patient has received for  $> 2$  weeks, pamidronate or zoledronate also acceptable

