## 7.3 Trial Compliance

### 7.3.1 Prior and Concomitant Therapy

#### 7.3.1.1 Prior Therapy

- 2 week washout from chemotherapy or corticosteroids
- 4 week washout from radiation therapy and/or immunotherapy
- No prior IL-15 permitted
- Bisphosphonates permitted.
- Prior doxorubicin is permitted
- NSAIDS permitted if patient requires for pain control and received for >2 weeks prior to Day 0
- All medications will be recorded in the study CRF
- Prior therapy will be reviewed during the screening process

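### Washout from prior radiation or immunotherapy is 2 weeks in Section 5.2 but 4 weeks in Section 7.3.1.1, so eligibility is undefined for dogs last treated about 15 to 27 days before Day 0

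*Protocol*

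**What the plan says.** Section 5.2 (Exclusion Criteria), item 4, excludes dogs with "Immunotherapy or radiation therapy within 2 weeks of Day 0". Section 7.3.1.1 (Prior Therapy) requires a "4 week washout from radiation therapy and/or immunotherapy". The same section adds that prior therapy is reviewed during screening, so its list bears on who is enrolled.

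The neighbouring entry in 7.3.1.1 reads "2 week washout from chemotherapy or corticosteroids". Its chemotherapy interval agrees with item 3 of Section 5.2, which also uses 2 weeks. Corticosteroids appear in 7.3.1.1 only.

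The primary endpoint in Section 3.2 is "Objective response rates based on radiographic response". Section 3.1 describes an open-label, non-randomised, single-arm trial. Section 8.1 sets the test: "Hypothesizing an improvement in ORR from 11% to 50% using conditioning chemotherapy", with the statement that "a sample size of 10 provides 80% power to detect this difference", one-sided at 0.05.

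**The concern.** Two current sections set different entry rules for the same therapies, and no sentence ranks one above the other or explains the difference. Two members of staff could follow the protocol faithfully and reach opposite decisions on the same dog.

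Such a dog can plausibly present. Section 5.1 requires local control of the primary tumour and names radiation as one route, and Section 5.2 anticipates prior immunotherapy. Section 5.4.1.1 applies the same criteria at re-screening, so the ambiguity recurs there.

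The statistical stake is attribution. With no concurrent control, any response on radiographs counts towards the response rate that is compared with 11%. The washout is the main protection against counting a response that belongs to an earlier treatment, and its length is not fixed for radiation and immunotherapy.

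**Working it through.** **1. The two rules side by side (Sections 5.2 and 7.3.1.1)**

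| Prior therapy | Section 5.2 | Section 7.3.1.1 | Agreement |
|---|---|---|---|
| Chemotherapy | 2 weeks | 2 weeks | yes |
| Radiation | 2 weeks | 4 weeks | no |
| Immunotherapy | 2 weeks | 4 weeks | no |
| Corticosteroids | not listed | 2 weeks | listed once only |

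Two weeks is 14 days and four weeks is 28 days. A last treatment on days 15 to 27 before Day 0 passes 5.2 and fails 7.3.1.1. Day 28 is a boundary case that depends on how the four weeks are counted.

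**2. The plan's own figure**

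Inputs from Section 8.1: n = 10, null rate 0.11, alternative 0.50, one-sided 0.05. With X the number of responders, the exact binomial tail is P(X ≥ r) = Σ from k = r to n of C(n,k) p^k (1−p)^(n−k).

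At p = 0.11 and n = 10: P(0) = 0.3118, P(1) = 0.3854, P(2) = 0.2143, P(3) = 0.0706.

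- P(X ≥ 3) = 1 − (0.3118 + 0.3854 + 0.2143) = 0.088, above 0.05.
- P(X ≥ 4) = 0.088 − 0.071 ≈ 0.018 (unrounded 0.0178), so the exact rule is 4 or more responses.
- Power at p = 0.50: 1 − (1 + 10 + 45 + 120)/1024 = 848/1024 = 0.828.

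Ten dogs therefore give at least the stated 80% power, and the sample size statement stands.

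**3. Effect of a carried-over response (assumption, not in the documents)**

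Suppose m of the 10 dogs are certain to respond because of earlier therapy and the others respond at 11%. The rule of 4 is then met if at least 4 − m of the other 10 − m respond.

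| m | Calculation | False-positive probability |
|---|---|---|
| 0 | P(X ≥ 4), n = 10 | 0.018 |
| 1 | P(X ≥ 3), n = 9 | 0.067 |
| 2 | P(X ≥ 2), n = 8 | 0.217 |

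The row m = 1 is the extreme for a single dog. If that dog responds with probability q instead, the false-positive probability is q × 0.0672 + (1 − q) × 0.0117, where 0.0117 is P(X ≥ 4) for n = 9. Setting q = 0.11 returns 0.018, as it should. The result exceeds 0.05 only when q > (0.05 − 0.0117)/(0.0672 − 0.0117) = 0.0383/0.0555 ≈ 0.69.

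**4. Effect of leaving out one dog**

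- From 4/10 (p = 0.018), leaving out a responder gives 3/9, p = 0.067.
- From 3/10 (p = 0.088), leaving out one non-responder also gives 3/9, p = 0.067, still above 0.05. Leaving out two gives 3/8, p = 0.049.

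**The case against.** **The two rules can be met together.** Any dog that satisfies four weeks also satisfies two, so a reader might apply both and see no practical conflict. That is a workable reading, but the protocol does not state it, and a screener working from the exclusion list alone would enrol the dog.

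**Carry-over is not shown.** This stands. The only prior radiation that the protocol describes is for control of the primary tumour, whereas dogs enter with pulmonary nodules of at least 1 cm and the Day 0 visit includes baseline radiographs, taken after any earlier therapy. Prior immunotherapy is the more plausible route, but the documents contain no figure for late responses or for how many dogs would fall in the window. Nor would agreeing an interval make a single-arm trial able to attribute responses with certainty.

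**The one-dog margin belongs to the sample size.** A reader might infer that the washout conflict makes the conclusion turn on one dog. The gap between 3/10 and 4/10 exists in any 10-dog test against 11%, so it does not measure this defect. Leaving out a single non-responder does not rescue 3/10 either.

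**After-the-fact exclusion.** A reader might also infer that Section 8.3 lets a disputed dog be kept or dropped as compliant once its outcome is known. The only criterion stated there is starting inhaled IL-15, which a dog in the window can meet. Section 7.3.4 sends deviations to a form and to the principal investigator's review, and no text makes a washout breach a ground for removal from analysis.

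**Corticosteroids.** Stating a washout in one section and omitting it from another is not a contradiction. Section 10.3 names an inclusion/exclusion form, but its content is not shown, so it cannot be said that the corticosteroid washout goes unchecked. Listing it with the others is a matter of tidiness.

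**Conclusion.** The protocol is wrong as written on this point. For radiation and immunotherapy it sets two different washouts in current text, and eligibility is undefined for a last treatment about 15 to 27 days before Day 0. That conclusion needs no assumption.

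The effect on the primary result is conditional. If a recent therapy caused a late response, this design could not separate it from the study regimen. One dog assumed certain to respond for that reason would take the false-positive probability from 0.018 to 0.067, and two would take it to 0.217. For a single dog the stated 0.05 is exceeded only if its chance of such a response is above about 0.69. These figures show how sensitive the test is. They do not estimate a bias, because the documents give neither the number of dogs affected nor the likelihood of a late response. The sample size of 10 is unaffected.

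**What to change.** Reconcile Section 5.2 item 4 with Section 7.3.1.1 so that each therapy class has one washout, stated identically in both places, with the counting rule for the boundary day made explicit. The interval is for the sponsor's clinicians to choose; the documents do not show which was intended. Carry the corticosteroid washout already given in 7.3.1.1 into the same eligibility list, and build the inclusion/exclusion form from that list.

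For any dog already enrolled in the disputed window, record the therapy and the days from last treatment to Day 0. Keep the main analysis set as Section 8.3 defines it, and report the response rate with and without these dogs as a sensitivity analysis, using the exact test at the actual denominator.

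The cost is a short amendment and an updated form. Accrual may be slower if the longer interval is kept.
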